### Sample size estimation

G*Power was used to determine the sample size. Based on the previous intervention studies, the most frequently reported effect size was ranged from moderate (0.25) to high (0.70) [28, 29], a moderate effect size of 0.25 will be adopted for the current study. To ensure a power of 80% probability for detecting a treatment difference at a two-sided 5% level of significance, a sample size of 35 participants per group (total 105 for 3 groups) is expected to recruit. Yet, considering a 20% of potential dropout rate, a sample size of 42 participants per group (total 126 for 3 groups) will be required in the current study for the two-way repeated measures in three-time points. It is decided a total of 126 participants will be recruited. In order to satisfy the culture of KSA that males and females should undergo walking intervention separately in the group, an equal number of males and females (63 M and 63 F) will be recruited and randomly and equally assigned to the two intervention groups and control group. Moreover, in order to have an approximate mean age in each intervention group, the participants will be divided into 2 groups (60–64 and 65 to 70) for the randomization.

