**Discussion:**

This study aims to determine whether supervised group walking and non-supervised individual walking lead to different effects. Given the limited evidence in the literature regarding Saudi Arabia older adults’ physical fitness and health, it is worthwhile to explore the effect of walking, as well as the forms of walking on improving the overall physical fitness and psychological status of older adults in Saudi Arabia. The findings of the current study could also create awareness of the government and the general public in Saudi Arabia of the ageing problems and the effective ways of achieving better intervention results.

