To compare the difference of effects between supervised group-based walking and non-supervised individual-based walking on the primary outcomes, including frailty, cognitive functions, and health-related quality of life among inactive older adults in Saudi Arabia.To compare the difference of effects between supervised group-based walking and non-supervised individual-based walking on the secondary outcomes, including physical activity enjoyment, health parameters consisting of resting heart rate, resting blood pressure, and body composition, as well as walking performance among inactive older adults in Saudi Arabia.To formulate guidelines for achieving an effective walking intervention for inactive older adults in Saudi Arabia.To recommend the government of Saudi Arabia on guidelines and policies for promoting walking and active ageing among older adults in the country.

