### Grouping and randomization

Qualified male (*n* = 63) and female (*n* = 63) participants who have signed a consent letter will be randomly assigned into the three groups by a draw of lots, in a ratio of 1:1. The three groups will be (1) Supervised Group-based Intervention (SGBI; *n* = 42); (2) Non-supervised Individual-based Intervention (NSIBI; *n* = 42) and (3) Control Group (CG) (*n* = 42). The CONSORT procedure [26](Schulz et al., 2010) will be followed for the assignment and collection of data (Fig. 1).

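### The stated 80% power is not shown to apply to the primary comparison of supervised group walking with unsupervised individual walking

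*Protocol article*

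**What the plan says.** Under Sample size estimation, the article says that "a moderate effect size of 0.25 will be adopted for the current study". The power statement reads: "To ensure a power of 80% probability for detecting a treatment difference at a two-sided 5% level of significance". The size given for this, before any allowance for dropout, is worded as follows: "a sample size of 35 participants per group (total 105 for 3 groups) is expected to recruit". After that allowance the article arrives at 42 per group and 126 in total, described as being "for the two-way repeated measures in three-time points". No pair of arms, pattern of means or within-person correlation is given.

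The first item in the list of objectives is "To compare the difference of effects between supervised group-based walking and non-supervised individual-based walking on the primary outcomes". The Discussion part of the abstract repeats the aim: "This study aims to determine whether supervised group walking and non-supervised individual walking lead to different effects". The closing Discussion and conclusion section does the same.

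The third arm is a control that receives no training until after the final assessment (Study design). Table 1 gives the two walking arms the same duration, intensity and step targets. Under Statistical analysis, the between-group test is an ANCOVA with the baseline value as covariate at each later visit, and the planned contrasts named are those of the interventions against control.

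**The concern.** The sample size paragraph has one effect size and three arms, while the primary question concerns two of them. If 0.25 is Cohen's f across three arms, it measures the spread of all three means. Walking against no walking can supply most or all of that spread, and the difference between the two forms of walking can then be anything from zero upwards at the same f.

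A reader will take the 80% as the power for the primary objective. The results are meant to inform guidelines and policy on professional trainers. If the real power for SGBI versus NSIBI is well below 80%, a non-significant result is likely even when supervision helps. Read against the printed figure, it would look like better evidence of no difference than it is.

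**Working it through.** **Inputs from the article:** effect size 0.25; two-sided 5%; 80% power; 35 per group (105) before and 42 per group (126) after the dropout allowance; three equal arms; three time points; baseline-adjusted ANCOVA.

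**Assumption:** the correlation between visits is not printed. I use 0.5 as the central value and show 0.3 to 0.7.

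**Step 1. Reproduce the printed size.** For the group effect in a repeated-measures ANOVA with m = 3 visits, λ = N f² m / (1 + (m − 1)ρ). With N = 105, f = 0.25 and ρ = 0.5, λ = 105 × 0.0625 × 3 / 2 = 9.84 on 2 and 102 df, and power is 79.7%. Strictly, 80% is first reached at 108 (36 per group). A correlation of 0.47 to 0.49 gives exactly 35 per group.

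Other readings tried do not give 105: one-way ANOVA needs 159, the group-by-time interaction 36, three-arm ANCOVA with r = 0.5 needs 120, and a plain two-sample test of 0.25 SD needs 252 per arm. One pairwise reading does fit. A two-arm repeated-measures group test with f = 0.25 and ρ = 0.3 has λ = 70 × 0.0625 × 3 / 1.6 = 8.20 and 80.6% power at 35 per group.

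**Step 2. What a three-arm f of 0.25 implies for SGBI versus NSIBI.** Here f is the SD of the three arm means divided by the within-arm SD.
- Evenly spaced (control, NSIBI, SGBI at −a, 0, a): f = a√(2/3), so a = 0.25 / 0.816 = 0.306 SD.
- NSIBI equal to control, SGBI different by d: f = d√2/3, so d = 0.25 × 3 / 1.414 = 0.530 SD.
- SGBI equal to NSIBI, both different from control: the pair differs by 0.
- SGBI and NSIBI at the extremes with control midway: 2a = 0.612 SD.

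**Step 3. Power for that pair.** For the baseline-adjusted contrast, the noncentrality is d / √(1 − r²) × √(n/2), with df = 3n − 4 = 101 and critical value 1.984. At n = 35 and r = 0.5, the evenly spaced case gives 0.306 / 0.866 × 4.183 = 1.48, and the case with NSIBI equal to control gives 2.56. The last column uses the average of three visits at ρ = 0.5, the model that nearly reproduces 105.

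| Pattern (difference) | ANCOVA r = 0.3 | r = 0.5 | r = 0.7 | Averaged visits, ρ = 0.5 |
|---|---|---|---|---|
| Evenly spaced (0.31 SD) | 26.5% | 31% | 43% | 34% |
| NSIBI = control (0.53 SD) | 63% | 72% | 87% | 77% |
| SGBI = NSIBI (0) | 5% | 5% | 5% | 5% |
| Control midway (0.61 SD) | 76% | 83% | 94% | 87% |

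If all 42 per arm were retained, ANCOVA at r = 0.5 would give 36% (evenly spaced) and 80% (NSIBI = control). The averaged model would give 40% and 84%.

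**Step 4. Detectable difference.** At 80% power, 35 per arm and r = 0.5: (1.984 + 0.845) × √(2/35) × √0.75 = 2.829 × 0.239 × 0.866 = 0.59 SD.

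**The case against.** The strongest reply is that the calculation may have been made for a pair of arms. The wording speaks of a single treatment difference, is two-sided, and gives the size per group before the total. As Step 1 shows, a two-arm repeated-measures test with ρ = 0.3 also needs 35 per group. This stands to the extent that the documents do not settle which test was run, so it cannot be asserted that the 80% belongs to the three-arm test.

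It does not carry the 80% over to the planned analysis. For two arms, f = 0.25 means d = 0.5. With 35 per arm, the baseline-adjusted ANCOVA then has 58% power at r = 0.3, 67% at 0.5 and 82–83% at 0.7. At the correlation that makes the pairwise reading fit, the planned test has 58%.

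A second reply is that an overall f fixes no pairwise difference, so any single power figure for SGBI versus NSIBI is a chosen scenario. That is correct. A reader might infer from Step 3 that the head-to-head power simply is 31%, or that 72% is its ceiling. Neither follows. The 31% belongs to one pattern of means at one assumed correlation. The 72% is exceeded with a higher correlation, with the averaged-visit model, with 42 per arm retained, or with control between the two walking arms.

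A third reply is that the article nowhere plans to read a non-significant result as equivalence. That is also true, and no such plan is alleged. The point concerns what the printed power invites readers to conclude.

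**Conclusion.** The point holds as a mismatch between the stated power and the stated primary question. The article attaches 80% to an unnamed comparison, and the printed size is closely, though not uniquely, matched by an overall three-arm test. Nothing in the article establishes 80% for SGBI versus NSIBI.

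If 0.25 is the three-arm f, power for that pair with 35 per arm and baseline adjustment is about 27–43% for evenly spaced arms and about 63–87% if NSIBI equals control, over assumed correlations of 0.3 to 0.7. It is 5% if the two walking arms are equally effective. The last result does not depend on the correlation: the overall f can be 0.25 while the primary difference is zero. The remaining figures depend on the unprinted correlation, the assumed pattern of means and 35 completers per arm. They show how far the 80% may be off and are not estimates of the trial's actual power.

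**What to change.** Keep N at 126 and revise the Sample size estimation paragraph:

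- State, from the G*Power run, which test, effect-size metric and correlation the 80% refers to. Do not present it as the power for SGBI versus NSIBI unless the run was for that pair.
- Give the power or the detectable difference for SGBI versus NSIBI under the planned baseline-adjusted analysis, labelled as depending on the assumed correlation. With 35 per arm and r = 0.5, the difference detectable with 80% power is about 0.59 SD.
- State that the head-to-head conclusion will rest on the estimated difference and its 95% CI.

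This costs a few sentences and needs no extra participants or assessments. The downside is a less favourable stated power for the primary objective.

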### Statistical analysis

Descriptive statistics will be used to describe baseline characteristics such as gender, age, living status (alone or with family), body height, body weight, resting heart rate, and blood pressure of the participants in the study. The primary outcomes will be analyzed using an intention-to-treat (ITT) approach, and a sensitivity test will subsequently be conducted using the available data. Missing data will be replaced using the last observation carried forward method. For the secondary outcomes, a per-protocol analysis will be conducted using the available data. The statistical significance level was set at *p* < .05. All data will be analyzed using SPSS Version 26.0 (IBM, Chicago, IL). For the within-group test, a one-way repeated measure analysis of variance (ANOVA) will be applied to each group to determine the changes of each outcome parameter among the three-time points (i.e., pretest, posttest, and follow-up test). When the sphericity assumption was violated, the Greenhouse– Geisser correction will be used when epsilon < 0.75, or the Huynh–Feldt correction will be used when epsilon > 0.75. Post hoc analysis with Bonferroni correction will be conducted to explore the differences between the pretest and posttest, as well as posttest and follow-up test. The mean differences with 95% confidence intervals (CIs) will be reported. For the inter-group test, a one-way analysis of covariance (ANCOVA) with the baseline value as a covariate will be conducted at the posttest, and follow-up test to determine the group effect on each outcome parameter. Subsequently, the differences between the intervention groups and the control group will be analyzed through planned contrasts.

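### 42 per group covers 16.7% dropout, not the stated 20%, and the 35 behind it is sized for a two-way repeated-measures test that the analysis section does not plan, so 80% power is not demonstrated for the planned ANCOVA

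*Protocol article*

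**What the plan says.** In the protocol article, Sample size estimation, the target is 80% power ("To ensure a power of 80% probability for detecting a treatment difference") "at a two-sided 5% level of significance", and "a moderate effect size of 0.25 will be adopted for the current study". The evaluable size follows: "a sample size of 35 participants per group (total 105 for 3 groups) is expected to recruit". It is then raised for attrition: "considering a 20% of potential dropout rate, a sample size of 42 participants per group (total 126 for 3 groups) will be required", and the sentence ends by naming the test, "for the two-way repeated measures in three-time points".

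The Statistical analysis section plans different tests. Within each group there is a one-way repeated-measures ANOVA over the three time points. Between groups, "a one-way analysis of covariance (ANCOVA) with the baseline value as a covariate will be conducted at the posttest, and follow-up test", followed by planned contrasts of the intervention groups against control. No two-way group-by-time model is listed.

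On who is analysed, the Statistical analysis section uses intention to treat with LOCF for the primary outcomes. The end of the intervention section instead limits the analyses to participants who attended at least 70% of sessions.

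**The concern.** There are two separate problems in one paragraph.

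- **Attrition.** Multiplying by 1 + 0.20 does not protect against a 20% loss; dividing by 1 − 0.20 does. On its own numbers, the paragraph promises a retained sample that it does not secure.
- **Basis of the power.** A repeated-measures test that uses all three time points does not have the same power as a baseline-adjusted comparison at a single time point. A power figure for the first says little about the second unless the baseline-to-outcome correlation is given, and it is not.

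The trial is meant to inform policy on professional supervision of walking. If readers take 80% power as established for the reported group comparisons, they may read a non-significant result as stronger evidence of no difference than it is.

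**Working it through.** **Inputs from the article:** α = 0.05, power 80%, effect size 0.25, three equal groups, three time points, 35 then 42 per group, 20% dropout. **Assumptions:** 0.25 is Cohen's f (the metric is not named), and the correlation r between measurements is not stated, so a range is shown.

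**1. Reproducing 105.** Power comes from the noncentral F distribution with noncentrality λ.

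- Group main effect of a repeated-measures ANOVA, r = 0.5: λ = f²·N·3/(1 + 2r) = 0.0625 × 105 × 3/2 = 9.84, df 2 and 102. Power is 79.7%. Reaching 80% needs 106, or 108 if balanced. This agrees with 105 within rounding.
- Group-by-time interaction under the alternative effect-size definition: λ = f²·(N − 3)·2 = 0.0625 × 102 × 2 = 12.75, df 4 and 204. Power is 81.9%. The smallest balanced N is 102. This also agrees.
- Interaction with r = 0.5 entered in λ: only 36 in total are needed. This does not agree.
- One-way ANOVA at a single time point: 159 in total are needed. This does not agree.

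So 105 fits a two-way repeated-measures test in either of two forms, consistent with the test the section names.

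**2. Dropout.**

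- 35 × 1.20 = 42, the stated figure.
- 35/(1 − 0.20) = 43.75, so 44 per group, 132 in total.
- 42 × 0.80 = 33.6 per group; 126 × 0.80 = 100.8 in total, against 105 needed.
- Loss that 42 tolerates: 1 − 35/42 = 16.7%.
- Power at 100.8 for the tests in step 1: main effect 77.9% (from 79.7%); interaction 80.0% (from 81.9%).

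**3. Power for the planned ANCOVA.** Omnibus test at one time point: λ = f²·N/(1 − r²), df 2 and N − 4, where r is the baseline-to-outcome correlation. For example, with N = 126 and r = 0.5, λ = 0.0625 × 126/0.75 = 10.5 and power is 82.5%.

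| r | N ≈ 101 (20% lost) | N = 105 | N = 126 (ITT with LOCF) |
|---|---|---|---|
| 0 | 59% | 61% | 70% |
| 0.3 | 64% | 65.5% | 74% |
| 0.5 | 73% | 74.5% | 82.5% |
| 0.6 | 80% | 81% | 88% |
| 0.7 | 88% | 90% | 94.5% |

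The last column ignores any bias or dilution from carrying observations forward.

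**4. Detectable difference for the first objective** (supervised group walking against unsupervised individual walking). With 33.6 per arm, r = 0.5 and two-sided 5%, the normal approximation gives (1.960 + 0.842) × √(2 × 0.75/33.6) = 0.59 SD. The t distribution raises this to about 0.60 SD.

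**The case against.** The strongest reply is that the primary analysis is by intention to treat with LOCF, so all 126 stay in and the dropout inflation hardly matters. At r = 0.5 the planned ANCOVA then has 82.5% power. This stands in part, and it limits the conclusion. It fails at low correlation (70% at r = 0, 74% at r = 0.3), and it sets aside LOCF bias. It also depends on an analysis set that the 70%-attendance restriction contradicts.

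A second reply is that the dropout slip is small. That is right: about two points on either reading, and on the interaction reading the power stays at 80.0%.

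Three stronger readings are tempting but not supported.

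- A reader might infer that the trial will not have 80% power. The correlation is not given, and power reaches 80% from about r = 0.6 with completers, and by r = 0.5 with all 126.
- A reader might infer that 105 can only have come from the group main effect. The interaction under the alternative definition fits as well.
- A reader might convert f = 0.25 to a 0.5 SD gap and quote a low power for the comparison of the two walking arms. That conversion belongs to a two-group design. The article states no such difference, and its planned contrasts are against control.

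**Conclusion.** The point holds as a should-fix. Two statements are wrong or inconsistent as written, and neither depends on an outside assumption: 42 per group does not preserve 35 after 20% dropout (it leaves 33.6 and covers 16.7%), and the test used for sizing is not among the tests planned.

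The consequence is that 80% power is not demonstrated for the planned ANCOVA, not that it is absent. At r from 0 to 0.6, omnibus power runs from 59% to 80% with about 101 completers and from 70% to 88% with all 126. These figures assume that 0.25 is Cohen's f and that the correlation lies in the range shown. Which column applies cannot be settled while the intention-to-treat statement and the attendance restriction disagree.

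**What to change.** Keep 126 participants and rewrite the sample size paragraph.

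- State that 42 per group covers 16.7% dropout and that about 33 per group remain at 20%. If 35 must be preserved at 20%, the figure is 44 per group (132).
- Replace the repeated-measures basis with power, or the detectable difference, for the planned one-way ANCOVA. State the baseline correlation as a range, and give results for both the intention-to-treat set and the completers.
- Say that 0.25 is Cohen's f, if that is what was meant.
- For the first objective, add the detectable difference between the two walking arms (about 0.60 SD at r = 0.5 with 33.6 per arm), and note that the analysis section does not currently list this contrast.

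The cost is one rewritten paragraph and possibly a less favourable stated power. No extra participants are needed.

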### Grouping and randomization

Qualified male (*n* = 63) and female (*n* = 63) participants who have signed a consent letter will be randomly assigned into the three groups by a draw of lots, in a ratio of 1:1. The three groups will be (1) Supervised Group-based Intervention (SGBI; *n* = 42); (2) Non-supervised Individual-based Intervention (NSIBI; *n* = 42) and (3) Control Group (CG) (*n* = 42). The CONSORT procedure [26](Schulz et al., 2010) will be followed for the assignment and collection of data (Fig. 1).

**Fig. 1 Fig1:**
[figure not shown]
CONSORT Diagram for participants recruitment and intervention

### The intervention

#### Prescription of walking intervention

The walking intervention will be conducted in duration of 16 weeks, with 3 sessions per week and 50–70 min per session. As respects to the culture of KSA, male and female participants will undergo intervention in separate groups, with supervision or assistance by professional trainers or research assistants in the same gender during the intervention. In intervention program, the ACSM progressive training principle will be adopted. The intensity and repetition will be progressively increased in accordance with the 4 levels as prescribed, in which weeks 1 to 4 are Level-1; weeks 5 to 8 are Level-2, weeks 9 to 12 are Level-3, weeks 13–16 are Level-4 (Please refer to Table 1 for the detailed intervention program). The levels of progression could ensure the physically inactive participants have sufficient time to equip with an appropriate base of fitness and familiar with regular walking regime, as well as to prevent musculoskeletal injuries and over training. Also, the design of the training sessions will include the expected target heart rates, the intensity and the expected number of steps. Most importantly, each participant will be required to put on a wrist-worn Fitbit Charge 3 to keep track of their exercise intensity levels, including their heart rate changes in relation to their target heart rate zones, and the accumulated amount of steps after each session. In addition to progression, the training principle of individuality will also be applied to the participants doing the walking. They will be allowed to complete the targeted steps based on their own targeted heart rates as well as physical conditions during walking. Participants are free to taking short breaks or withdraw from walking if they uncomfortable doing it according to the schedule. Furthermore, in order to minimize the external influences caused by environmental settings, both intervention groups will receive the training at the same indoor track/sports paradise, with air-conditioning to produce a constant temperature.

**Table 1 Tab1:** Intervention Protocol (Coswig et al., 2020 ; Harris et al., 2017; Haynes et al., 2020; Ignaszewski et al., 2017;Tudor-Locke et al., 2018)

Intervention Group	SGBI	NSIBI
Condition Warm-up (stretching): 5–10 min Walking: 20-40 min Cool-down (stretching): 5-10 min	Supervised group-based intervention Manpower: Research Assistant & Qualified Fitness Trainer Equipment: Fitbit Charge 3 Venue: Indoor Sport Paradise	Non-supervised individual-based intervention Manpower: Research Assistant Equipment: Fitbit Charge 3 Venue: Indoor Sport Paradise
**Level-1** **1–4 Weeks** **Low-to-Moderate Intensity**	**Duration**: 50 min. 3 times per week **Expected Intensity**: 50–60% of HRmax **Targeted steps**:3000/session **Parameters**: Heart rate Total number of steps	**Duration**: 50 min. 3 times per week **Expected Intensity**: 50–60% of HRmax **Targeted steps**:3000/session **Parameters**: Heart rate Total number of steps
**Level - 2** **5–8 Weeks** **Moderate Intensity**	**Duration**: 60 min. 3 times per week **Expected Intensity**: 50–60% of HRmax **Targeted steps**:4500/session **Parameters**: Heart rate Total number of steps	**Duration**: 60 min. 3 times per week **Expected Intensity**: 50–60% of HRmax **Targeted steps**:4500/session **Parameters**: Heart rate Total number of steps
**Level-3** **9-12 Weeks** **Moderate-to-high Intensity**	**Duration**: 60 min. 3 times per week **Expected Intensity**: 55–65% of HRmax **Targeted steps**:7000/session **Parameters**: Heart rate Total number of steps	**Duration**: 60 min. 3 times per week **Expected Intensity**: 55–65% of HRmax **Targeted steps**:7000/session **Parameters**: Heart rate Total number of steps
**Level-4** **13–16 Weeks** **Moderate-to-vigorous Intensity**	**Duration**: 70 min. 3 times per week **Expected Intensity**: 65–80% of HRmax **Targeted steps**:8500–10,000/session **Parameters**: Heart rate Total number of steps	**Duration**: 70 min. 3 times per week **Expected Intensity**: 65–80% of HRmax **Targeted steps**:8500–10,000/session **Parameters**: Heart rate Total number of steps

Additionally, to respect the culture of KSA, male and female participants will be separated to undergo the walking intervention. In such arrangement, there will be 4 groups [2 groups (1 male and 1 female) under group-based and 2 groups (1 male and 1 female) under individual-based] and each group will have 21 participants when doing walking. While qualified professional fitness trainers (1 male and 1 female separately for male and female groups, respectively) will be involved in the group-based intervention programs in order to provide appropriate guidance and supervision to the participants. Whereas, the non-supervised individual-based intervention will be conducted by a research assistant (males and females) to ensure the attendance and general safety, but without providing professional advice or supervision.

Upon completion of the 16-week walking interventions, only data of the participants who have attended at least 70% of the training sessions will be included in the analyses.

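### Supervised walking is delivered in two classes of 21, but the power and the ANCOVA assume independent participants; if outcomes correlate within class, intervals for supervised-arm contrasts are too narrow and power is overstated

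*Protocol article*

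**What the plan says.** Under Grouping and randomization, individuals are allocated by lot, within sex, to SGBI, the non-supervised individual-based arm (NSIBI) or control, 42 per arm. Prescription of walking intervention then splits each walking arm into one male and one female group, and "each group will have 21 participants when doing walking". The supervised groups have "qualified professional fitness trainers (1 male and 1 female separately for male and female groups, respectively"). The NSIBI sessions are run by a research assistant, who sees to attendance and general safety and gives no professional advice or supervision. The control group has no sessions.

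Design of intervention programs describes group exercise as working through group dynamics, cohesiveness and social support. Benefits of group-based physical activity makes the same case.

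Sample size estimation states: "To ensure a power of 80% probability for detecting a treatment difference at a two-sided 5% level of significance", that "a moderate effect size of 0.25 will be adopted for the current study", and that "a sample size of 35 participants per group (total 105 for 3 groups) is expected to recruit". A 20% dropout allowance raises this to 42 per arm (126 in total). No ICC or design effect is given. For the comparison between arms, Statistical analysis says that "a one-way analysis of covariance (ANCOVA) with the baseline value as a covariate will be conducted" at posttest and at follow-up. The baseline value is the only covariate named; there is no term for class, trainer or sex.

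**The concern.** People who train together three times a week for 16 weeks under one trainer share that trainer's skill and the social climate of their class. The protocol counts on exactly these influences to make supervised group walking work. The same influences would make the outcomes of class members resemble each other. The variance of the SGBI mean would then exceed what 42 (or 35) independent people would give, while the control mean would be unaffected. This is a partially nested design.

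A one-way ANCOVA that ignores the nesting would give standard errors for SGBI contrasts that are too small, intervals that cover less than 95%, and tests that reject more than 5% of the time under the null. The comparison of SGBI with NSIBI, the first objective, is affected. With only two trainers in the supervised arm, a benefit due to two good trainers would look the same as a benefit of supervised group walking. That matters because the authors mean to use the result to argue for trainer staffing and public guidelines.

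**Working it through.** **Inputs from the protocol.** Effect size 0.25 (taken as Cohen's f, since the metric is not named), two-sided 5%, power 80%, 3 arms, 3 time points, 35 per arm before dropout (105), 42 recruited (126), walking groups of 21, two per walking arm.

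**Assumptions.** Correlation between time points 0.5. ICC 0.01, 0.02 and 0.05. Analysed class size m = 35/2 = 17.5.

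**Step 1: reproduce the stated sample size.** For the between-arm effect in a repeated-measures ANOVA, the noncentrality is λ = f² × N × 3 / (1 + 2ρ). With f = 0.25, N = 105 and ρ = 0.5, λ = 0.0625 × 105 × 3/2 = 9.84. On 2 and 102 degrees of freedom this gives power 0.797. The smallest balanced N that reaches 80% is 108. So 105 is reproduced to within 3% by a calculation with independent participants and no allowance for clustering.

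**Step 2: design effect in a clustered arm.** DE = 1 + (m − 1) × ICC = 1 + 16.5 × ICC, and effective n = 35/DE.

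| ICC | DE | Effective n (of 35) |
|---|---|---|
| 0.01 | 1.17 | 30 |
| 0.02 | 1.33 | 26 |
| 0.05 | 1.83 | 19 |

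**Step 3: true level of a nominal 5% test.** With SGBI clustered and the other arm not, the variance of the contrast is inflated by (DE + 1)/2. With both arms clustered equally it is inflated by DE. In each case the level is 2 × [1 − Φ(1.96/√inflation)].

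| ICC | SGBI clustered: SE ratio | Level | Both walking arms clustered: SE ratio | Level (SGBI vs NSIBI) |
|---|---|---|---|---|
| 0.01 | 1.04 | 6.0% | 1.08 | 6.9% |
| 0.02 | 1.08 | 6.9% | 1.15 | 8.9% |
| 0.05 | 1.19 | 9.9% | 1.35 | 14.7% |

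Coverage of the nominal 95% interval is 100% minus the level: about 94%, 93% and 90% with only SGBI clustered.

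**Step 4: power on the basis of Step 1.** Divide λ = 9.84 by the average variance inflation over the three arms: (DE + 2)/3 if only SGBI is clustered, (2DE + 1)/3 if both walking arms are.

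| ICC | λ, SGBI only | Power | λ, both | Power |
|---|---|---|---|---|
| 0 | 9.84 | 80% | 9.84 | 80% |
| 0.01 | 9.33 | 77% | 8.87 | 75% |
| 0.02 | 8.87 | 75% | 8.07 | 71% |
| 0.05 | 7.72 | 69% | 6.35 | 60% |

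Averaging the inflation is an approximation. Summing effective sample sizes instead (35 + 35 + 35/DE) gives 78%, 76% and 72% with only SGBI clustered, so the direction and rough size do not depend on that choice.

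**The case against.** **The ICC is not known.** The protocol gives none for the SF-36, the Physical Performance Test or the MMSE, and the intervals are too narrow only if it exceeds zero. This stands. A reader might infer that the planned intervals are certainly too narrow; the document does not show that. It shows that the plan relies on a mechanism that would produce a positive ICC and leaves it out of the variance.

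**NSIBI is not a led class.** Its assistant oversees attendance and safety, participants walk to their own heart-rate and step targets, and the group-dynamics argument is made for group exercise. This also stands. One might read the four groups of 21 as four equally clustered classes, but the text supports clustering firmly only for SGBI. The figures with both walking arms clustered are therefore a second scenario.

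**Who is analysed.** Carrying the last observation forward under intention-to-treat could keep up to 42 per arm. By the method of Step 4, with m = 21 and only SGBI clustered, power would then be 85%, 82% and 75%, against 87% without clustering. So at 42 analysed the power drops below 80% only at the largest ICC. The test level is slightly worse, because the classes are larger.

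**Sex is left out of the ANCOVA.** Arms are balanced on sex, so omitting it tends to widen intervals and could offset some of the narrowing. True, but the offset is accidental and of unknown size. Within an arm sex and class coincide, so a sex term would not supply the missing between-class variance.

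**Two classes cannot estimate an ICC.** A random class effect would be very poorly estimated: the t critical value on 2 degrees of freedom is 4.30. That rules out a random-effects model as the remedy, but not a table at fixed ICC values.

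**This belongs in the analysis plan.** A sensitivity table often does. But the article itself fixes the test, its covariate and the basis of the power, and it is those stated choices that assume independence.

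**Conclusion.** The concern holds in conditional form. The 80% power and the named ANCOVA treat participants as independent, although SGBI is delivered in two classes with one trainer each and is expected to work through group and trainer. If outcomes correlate within class, SGBI contrasts are reported too precisely and the power is overstated.

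Over assumed ICCs of 0.01 to 0.05, with 35 analysed per arm, the understatement of the standard error is modest at the low end and material at the high end (4% to 19% with only SGBI clustered). These sizes rest on the assumed ICCs, an assumed correlation of 0.5 between time points and reading 0.25 as Cohen's f.

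The NSIBI versus control contrast is not shown to be affected unless NSIBI is also clustered. Nor does the document support the inference that a difference should count only if it survives an assumed ICC, because no ICC in the range has a basis in the text.

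**What to change.** 1. In Statistical analysis, add a sensitivity analysis that reports the SGBI contrasts with the variance of the SGBI mean multiplied by 1 + (m − 1) × ICC over a stated range, for example 0.01, 0.02 and 0.05, where m is the class size analysed. As a second scenario, inflate the NSIBI mean as well. Report the results beside the primary result, not as a pass/fail rule.
2. In Sample size estimation, say that the 80% assumes independent participants, and give the power over the same ICC range.
3. State that, with one trainer per supervised class, an effect of these particular trainers or classes cannot be separated from an effect of supervised group walking.

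The cost is a short table, a less favourable power figure and a sentence limiting the inference. It needs no more participants, classes or trainers and no change to the intervention.
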